# METHODOLOGY

**Inclusion Criteria**

- aged over 18 years,
- BMI over 30kg/m2, or over 28kg/m2 with comorbidities
- Speaks, reads, and understands English

**Exclusion Criteria**

- Medical condition precluding fasting, including a history of eating disorders;
- serious illness;
- currently on psychiatric medication;
- pregnancy or breastfeeding;
- has lost more than 5% of body weight in the last 6 months
- currently using TRE or another fasting approach to weight loss.

**Study Design**

Cohort follow-up.

**Study Scheme Diagram**

| **Recruitment**  Potential participants contact the study team via phone/email after seeing study ads and are screened. If eligible, they receive appointment and are sent the Participant Information Sheet (PIS). | | | | | | | |
| --- | --- | --- | --- | --- | --- | --- | --- |
|  |  | | |  | |  |  |
| **Baseline visit**  Informed consent; baseline questionnaires and measures of weight, BMI, blood pressure (BP) and lipid profile. TRE instructions given. | | | | | | | |
|  | |  |  |  |  | |  |
| **Week 1 Visit:** Participants will attend the clinic to give their weight and report on progress. | | | | | | | |
|  | | | |  | | | |
| **Weeks 2 to 5 Phone calls:** Participants will be called to check on their progress, and to collect data on self-reported weight and adherence. | | | | | | | |
|  | | | |  | | | |
| **Week 6 Visit:** Participants will attend the clinic to give their weight and report on their progress. | | | | | | | |
|  | | | |  | | | |
| **Week 12 visit:** Participants will attend the clinic to report on their progress. Measures of weight, BP, and limpid profile will be taken | | | | | | | |

**6 month follow up visit:** Participants will attend the clinic to give their weight, BP and report on their progress.

# STUDY PROCEDURES

**Participant recruitment**

Participants will be recruited via the following methods; advertising in newspapers including the Evening Standard, Metro and local papers; adverts on social media and on internet fora; online bulletins; leaflets and posters in community venues; leaflets via mail drops; and through our community weight clinic.

Prospective participants will contact the study team by telephone or e-mail. They will be screened and if eligible, will receive an appointment for the baseline visit and PIS will be sent by post or e-mail.

**Baseline Visit**

At the baseline visit, after completing the consent procedures, eligible participants will complete study questionnaires (see details below), and measurements of weight, blood pressure and a blood sample for lipid profile will be collected. Participants will than receive an explanation of the TRE intervention and of the follow-up procedures and the TRE diary.

**TRE intervention**

Participants will be asked to consume all their food during an 8 hour period each day for the next three months. Over the remaining 16 hours each day, participants can drink, but only non-calorie drinks (e.g. water or coffee/tea with no milk or sugar). Participants will be free to choose which 8-hour period they would like to eat in.

**Follow-up visits and calls:** Participants will attend at one and six weeks, to provide measures of weight and to discuss their progress. They will also receive phone calls at weeks 2, 3, 4 and 5, that will monitor progress and collect data on adherence.

**12 week follow-up visit**: Participants will attend at 12 weeks to provide measures of weight and blood pressure, and a blood sample for lipid profile and to report on their adherence to TRE and provide TRE ratings.

**Final follow up visit:** Participants will attend at 6 months to provide measures of weight and blood pressure, and to report on their adherence to TRE and provide the final TRE ratings.

Participants will receive £10 at the 6, 12 week and 6 month visits as a compensation for their time and travel. Participants providing a blood sample at baseline and 12 weeks, will also receive £10 for each sample given.

**Measures**

***Baseline:***

- Demographic information collected via routine clinic questionnaires
- Weight, BMI
- Blood pressure
- Blood lipid profile
- Physical activity levels (IPAQ)

***Weekly:***

- Weight (Week 1 and 6 only)
- Number of days on which TRE was adhered to
- 8-hour time periods selected.
- Ratings of TRE helpfulness, TRE difficulty, ratings of hunger on days TRE was adhered to
- Comments on TRE barriers and facilitators (Week 1 and 6 only)

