**Primary Outcome**

The primary outcome is the adherence to TRE over a period of 3 months, specifically the average number of days on which TRE was adhered to. We will also monitor the retention rates at 6 weeks, three months and 6 months, defined as the proportion of participants who adhere to TRE at least once a week; and the drop-out rate defined as the proportion of participants who do not attend the 3 month follow-up session. We will compare retention and drop-out rates with those in our previous trials and community clinics.

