**Secondary Outcomes**

- Changes in weight from baseline to 6 weeks, and to 3 months and 6 months.
- Changes in blood pressure from baseline to 3 months and 6 months,
- Changes in lipid profile from baseline to 3 months;
- Participant feedback and ratings of the intervention, including the helpfulness of the intervention, recommending it to friends, readiness to continue, barriers and facilitators, and most popular 8-hour time frames.
- Changes in ratings of the difficulty adhering to TRE and ratings of hunger over time
- Estimates of effect size for future randomised trials, if TRE is deemed feasible and efficacy is encouraging.
- Comparison of weight changes in TRE to weight changes in other weight-loss cohorts in our previous trials and community clinics.

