***Follow-up at 12 weeks:***

- Weight
- Blood pressure
- Blood Lipid profile
- IPAQ
- TRE adherence
- TRE ratings (helpfulness, difficulty, ratings of hunger, would recommend TRE to friends, barriers and facilitators)

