# STATISTICAL CONSIDERATIONS

**Sample Size**

In this early phase exploratory research, we opted for a pragmatic sample size of 50, achievable economically and quickly, but large enough to provide reasonable confidence intervals on key estimates.

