## Sample Analysis

A full Lipid profile will be obtained, including Total Cholesterol, Triglycerides and HDL Cholesterol. Total Cholesterol and Triglycerides will be analysed using the enzymatic, colorimetric method; and HDL Cholesterol with the homogeneous enzymatic colorimetric test.

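### Hunger is rated on TRE-adherent days at some visits and without that limit at 12 weeks, and no fasting state or draw time is fixed for the paired lipid samples, so either before-after change can be a product of measurement

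*Protocol*

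**What the plan says.** **Hunger.** The Secondary Outcomes section of the Protocol lists "Changes in ratings of the difficulty adhering to TRE and ratings of hunger over time". The Measures section says how the ratings are collected, and not in the same way at each visit:

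- Weekly list: "Ratings of TRE helpfulness, TRE difficulty, ratings of hunger on days TRE was adhered to".
- 12-week list: "TRE ratings (helpfulness, difficulty, ratings of hunger, would recommend TRE to friends, barriers and facilitators", with no reference to adherent days.
- 6-month list: the adherent-day limit returns, in the same words as the weekly list: "ratings of hunger on days TRE was adhered to".

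The baseline list has no hunger item, and the Schedule of Assessment starts ratings at week 1. Adherence is itself the primary outcome, "specifically the average number of days on which TRE was adhered to", so the number of rated days is expected to vary.

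**Lipids.** Under Study Procedures, the first sample is taken at the baseline visit before TRE is explained, and the second at 12 weeks while participants are on TRE. TRE means 16 hours a day without calories, and "Participants will be free to choose which 8-hour period they would like to eat in". Neither visit description gives a fasting state or a time of day. The Laboratories section leaves collection to the laboratory's own instructions, which are not shown, and the sample label carries an ID, a time point and a date. "A full Lipid profile will be obtained, including Total Cholesterol, Triglycerides and HDL Cholesterol". The Statistical Analysis section tests lipid change with a paired t-test; there is no concurrent control group.

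**The concern.** These are two separate measurement problems that share one consequence: a before-after change can arise without any change in the participant.

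For hunger, the rated days are selected by adherence. Hunger is a plausible reason for eating outside the window. If adherence declines and the hungriest days are the ones lost, the remaining ratings come increasingly from easier days and the series suggests that TRE becomes easier. No analysis can restore ratings that were never collected. The different wording at 12 weeks adds to this, because a series that changes definition midway cannot be read as a trend.

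For lipids, the intervention changes the time since last calories, and this is a condition under which the second sample is taken. If the share of participants fasted differs between the two draws, the paired difference includes that shift and no control arm removes it. The Secondary Objectives make encouraging efficacy results a condition for producing effect estimates for a future randomised trial. An artefact in lipid change could therefore feed into that judgement.

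**Working it through.** The Protocol gives no effect size, SD, power or alpha. On size it says only "we opted for a pragmatic sample size of 50", so there is no planned figure to reproduce. The checks below ask what each measurement rule yields when the true change is zero. N = 50 is from the Protocol. Everything else is an assumption, shown as a range, with two-sided alpha 0.05.

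**Hunger, limiting case.** Suppose daily hunger is normal and constant over time, and every non-adherent day is one of the hungriest. With a proportion p of days rated, mean rated hunger is −φ(z_p)/p, in SDs of daily hunger.

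- 6 of 7 days: p = 0.857, mean −0.263
- 3 of 7 days: p = 0.429, mean −0.916
- Change: −0.916 − (−0.263) = −0.653 SD

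**Hunger, probabilistic selection.** Person SD 1, day SD 1, both constant over time. The chance of adhering on a day is logistic with slope −b on that day's hunger. Mean hunger on adherent days is compared within person between an early and a late week of 7 days. Early adherence is 85% of days.

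| Late adherence | Change, b = 0.5 | Significant fall | Change, b = 1.0 | Significant fall |
|---|---|---|---|---|
| 85% | 0.00 | 2.7% | 0.00 | 2.7% |
| 70% | −0.07 | 13% | −0.12 | 28% |
| 50% | −0.16 | 33% | −0.29 | 83% |
| 30% | −0.26 | 51% | −0.46 | 95% |

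With b = 0 (adherence unrelated to hunger) the change is about 0 and a significant fall occurs in 2.3% to 2.9% of trials, against a nominal 2.5%. The percentages show how the shift compares with sampling error under a paired t-test. The Protocol names no test for hunger, so they are not error rates of a planned analysis. If each week is instead summarised over whoever has a rating, the shifts run from −0.07 to −0.64 units, because people with no adherent day drop out of the later mean.

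**Lipids.** Take the SD of the paired change as 1. Let a non-fasting sample read δ higher than a fasting one, and let the fasted shares be f0 at baseline and f1 at 12 weeks. With no true change, the expected paired difference is δ(f0 − f1). For f0 = 0.3 and f1 = 0.8 this is −0.5δ.

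| Fasted share, baseline to 12 weeks | Significant result | δ = 0.25 | δ = 0.5 | δ = 1.0 |
|---|---|---|---|---|
| 30% to 80% | false improvement | 14% | 38% | 83% |
| 30% to 50% | false improvement | 5% | 9% | 21% |
| 50% to 30% | false worsening | 5% | 10% | 21% |

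In the third row, false improvement occurs in 1% or less. With equal shares (30% and 30%) the mean change is about 0 and false improvement occurs in 2.3% to 2.5% of trials.

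**The case against.** Several points on the other side are sound.

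- A reader might infer that hunger is never rated on non-adherent days. The 12-week list does not support that, since it carries no limit. What stands is that the three lists differ and need to be reconciled.
- Hunger on adherent days can be a deliberate tolerability measure of how hard TRE is when practised. That is a fair use. It describes the days on which TRE was kept, though, and its trend is not a trend in hunger once adherence moves.
- A reader might treat the missing baseline hunger rating as an error. It contradicts nothing: the outcome is change over time, not change from baseline, and it is paired with difficulty of adhering, which cannot exist before TRE starts.
- The Statistical Analysis section assigns participants' ratings to description, so a false significant hunger result is not a planned output. A misleading descriptive trend remains possible.
- The 0.65 SD figure requires every lost day to be among the hungriest. It is a limit, not an expectation.
- A reader might infer that lipid samples will be taken in unmatched fasting states. The Protocol does not say so, and the unseen laboratory instructions may set a fasting rule. A TRE diary is issued and eating windows are recorded weekly and at 6 months, which gives partial information. The 12-week list does not repeat the windows, however, and no list asks for time of last food.
- The lipid bias has no fixed direction, because participants choose their window and its position relative to the visit is uncontrolled.

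**Conclusion.** The point holds in a limited form.

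For hunger, the weekly and 6-month rule selects the rated days by adherence, and the 12-week list is worded differently, while the outcome is a trend over time. A spurious fall needs two conditions: adherence declines, and hungrier days are the ones lost. Under probabilistic selection the within-person shift is about 0.07 to 0.46 units (day SD 1). Under perfect selection with adherence falling from 6 to 3 days a week it is 0.65 SD. With stable adherence it is nil. The slopes and adherence levels are assumed.

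For lipids, the supportable statement is that the Protocol itself secures no match in fasting state, draw time or time since last calories, in an uncontrolled paired comparison where the intervention changes the last of these. The effect is assumed to fall mainly on triglycerides, and its size cannot be taken from the document. It favours TRE only if more participants are fasted at 12 weeks than at baseline, and it reverses if fewer are. The stronger conclusion, that both outcomes will look better than they are, does not follow.

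Both are secondary outcomes. Adherence and retention, on which the feasibility objective rests, are untouched. The changes are still worth making before data collection, because neither gap can be filled afterwards.

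**What to change.** **Hunger.** Rate hunger on all days, adherent or not, and define the rating identically at weeks 1 to 6, 12 weeks and 6 months. Reconcile the three Measures lists accordingly. Keep the adherent-day rating and report it alongside as a description of tolerability, together with the number of adherent days behind it. A baseline hunger item is optional.

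**Lipids.** State in the Protocol the conditions for both draws: the same fasting condition and the same clock time where possible. If the laboratory instructions already set a fasting rule, cite it. Record the time of last caloric intake at both draws, so that any mismatch can be seen and examined.

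**Cost.** A wording change and a rating for non-adherent days on the CRF, one extra field on the sample log, and slightly less flexible appointment booking. The sample size and the primary outcome do not change.

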***Follow-up at 12 weeks:***

- Weight
- Blood pressure
- Blood Lipid profile
- IPAQ
- TRE adherence
- TRE ratings (helpfulness, difficulty, ratings of hunger, would recommend TRE to friends, barriers and facilitators)

***Final follow up at 6 months:***

- Weight
- Blood Pressure
- Number of weeks on which TRE was adhered to
- 8-hour time periods selected.
- Ratings of TRE helpfulness, TRE difficulty, ratings of hunger on days TRE was adhered to

**Subject withdrawal**

Participants will be able to stop the TRE intervention at any time. Participants who stop the intervention will be followed up at 6 weeks and 3 months, unless they do not wish to be.

Unless withdrawn participants request otherwise, data collected up to the point of their withdrawal will be used in the study analysis. Withdrawn participants will not be replaced.

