**End of Study Definition**

The study would be completed and the REC informed after the final attempt to collect 6-month follow-up data from the last participant.

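### The withdrawal section omits the 6-month visit for participants who stop TRE, in conflict with the sections that make 6 months an outcome time for participants generally

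*Protocol*

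**What the plan says.** The Subject withdrawal section is the only place in the Protocol that sets follow-up for people who give up TRE. It allows stopping whenever the participant chooses ("Participants will be able to stop the TRE intervention at any time") and then states: "Participants who stop the intervention will be followed up at 6 weeks and 3 months, unless they do not wish to be". Six months is not listed. The next paragraph turns to withdrawn participants and says that, unless they ask otherwise, "data collected up to the point of their withdrawal will be used in the study analysis".

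Other sections treat 6 months as an outcome time:

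- Secondary Outcomes lists "Changes in weight from baseline to 6 weeks, and to 3 months and 6 months" and "Changes in blood pressure from baseline to 3 months and 6 months".
- The final follow-up paragraph under TRE intervention says "Participants will attend at 6 months to provide measures of weight and blood pressure", with no condition on adherence. The Study Scheme Diagram describes the same visit.
- The 6-month list under Measures and the 6-month column of the Schedule of Assessment include weight, blood pressure and adherence.
- Primary Outcome includes retention at 6 months, counted as the share of participants who keep to TRE on at least one day a week.
- End of Study Definition closes the study "after the final attempt to collect 6-month follow-up data from the last participant".

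The prescribed intervention is shorter than the follow-up: "Participants will be asked to consume all their food during an 8 hour period each day for the next three months".

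**The concern.** The specific rule for stoppers and the general description of the 6-month visit do not agree. Staff dealing with someone who has stopped could reasonably apply the specific rule and not arrange a 6-month visit.

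Three features of the study make this matter. It has a single arm, so no control group shares the selection. Statistical Analysis specifies paired t-tests, which use only people measured at both times. The results are meant to supply effect estimates for a future randomised trial. Stoppers who attend at 3 months would be in the 3-month mean but absent from the 6-month mean, so a difference between the two could reflect who was measured and not what happened to their weight.

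Six-month retention has a related problem. If stoppers are not contacted, their status has to be assumed, or they drop out of the denominator.

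Whether a visit is attempted is a data-collection rule that belongs in the protocol. An analysis plan can say how missing values are handled but cannot supply measurements that were not sought.

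**Working it through.** **No stated figure to reproduce.** Sample Size gives 50 as a pragmatic number. The Protocol gives no expected stopping rate, weight change or standard deviation (SD). The stopping shares and weight differences below are therefore assumptions, used only to show scale.

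**Visits set side by side**

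| Section | Who | Visits |
|---|---|---|
| Subject withdrawal | Those who stop TRE | 6 weeks, 3 months |
| TRE intervention; Study Scheme Diagram | Participants, no adherence condition | Includes 6 months |
| Schedule of Assessment | No subgroup named | Includes 6 months |
| End of Study Definition | Up to the last participant | Ends after the last 6-month attempt |

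**Bias in the 6-month mean if stoppers are not measured.** Let s be the share who stop and are not measured, and g the mean loss in those measured minus the mean loss in those not measured.

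- Mean loss in everyone = (1 − s) × (loss in measured) + s × (loss in not measured).
- Observed mean loss = loss in measured.
- Overstatement = observed − everyone = s × g.

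| s (assumed) | g = 0 kg | g = 2 kg | g = 4 kg |
|---|---|---|---|
| 10% | 0 | 0.2 kg | 0.4 kg |
| 30% | 0 | 0.6 kg | 1.2 kg |
| 50% | 0 | 1.0 kg | 2.0 kg |

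For example, 0.30 × 2 = 0.6 kg. If stoppers did better than the rest, g is negative and the benefit is understated. The same formula applies to blood pressure.

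**Precision.** The 95% confidence interval half-width for a mean change is 1.96 × SD / √n.

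- n = 50: 1.96/√50 = 0.277 SD
- n = 45 (s = 10%): 0.292 SD
- n = 35 (s = 30%): 0.331 SD
- n = 25 (s = 50%): 0.392 SD

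**Retention.** If R participants meet the weekly definition at 6 months and no stopper has resumed, retention is R/50 with everyone counted and R/[50(1 − s)] with stoppers left out. The second exceeds the first by a factor of 1/(1 − s), which is 50/35 = 1.43 at s = 30%.

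**What is not affected.** The primary outcome is adherence over 3 months, and stoppers are expressly followed to 3 months. The 3-month weight and blood pressure changes, the lipid changes (3 months only) and the drop-out rate (defined by the 3-month visit) do not depend on the omitted visit.

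**The case against.** The strongest reply is that the withdrawal sentence neither says that follow-up ends at 3 months nor bars a later visit. The general text on the 6-month visit carries no adherence condition, and the study stays open until the last 6-month attempt. On that reading everyone is invited and the withdrawal sentence is merely incomplete. This is a fair reading, and it means the Protocol is inconsistent; a deliberate exclusion is not established. It does not remove the need to correct the sentence, which remains the only specific instruction for stoppers.

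A reader might go further and infer that the 6-month results would come from people still fasting. The Protocol does not support that. TRE is prescribed for three months, so someone who completes that period and then eases off has not clearly stopped the intervention and would be expected at 6 months. The 6-month measures also record how many weeks TRE was followed, and the retention definition presupposes that adherence varies at that visit. At most, the group missing is those who stopped during the intervention period.

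A reader might also take the withdrawal paragraph to mean that data collected after stopping TRE are discarded. The section schedules visits after stopping, so that is unlikely to be intended. Moving from stopping to withdrawal without separating the two is a wording ambiguity and no more.

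Two further points stand in part. Known stoppers could be counted as not retained without a visit, although any who resumed TRE would be missed. Missing-data handling may be set out in an analysis plan that is not at hand, so its absence from the Protocol is not criticised here.

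**Conclusion.** The inconsistency is real and should be fixed, but it does not threaten the study's main result. If the withdrawal rule is applied as written, the 6-month weight and blood pressure analyses omit those who stopped during the three-month intervention, are not comparable with the 3-month analyses, and could overstate benefit. The overstatement requires stoppers to have done worse, which is plausible but cannot be derived from the Protocol.

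Nor can its size. With assumed stopping of 10% to 50% and an assumed difference of 0 to 4 kg, the bias ranges from 0 to 2.0 kg; 30% and 2 kg give 0.6 kg. These figures take all non-stoppers as attending at 6 months and no stopper as attending. A statement that the benefit would be overstated by some given percentage goes beyond what the documents support.

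**What to change.** Amend the Subject withdrawal section so that participants who stop TRE are invited at 6 weeks, 3 months and 6 months unless they decline follow-up. In the same amendment:

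- separate stopping TRE from withdrawing from the study, and state that data collected after stopping TRE are used in the analysis;
- state that everyone who stopped remains in the denominator for 6-month retention.

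The cost is a short amendment, plus one visit that is already scheduled and its existing £10 payment per stopper. At an assumed 30% stopping, that is 15 × £10 = £150.

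If stoppers are deliberately not followed to 6 months, say so in the sections describing that visit, and label the 6-month results as coming from participants who did not stop during the intervention period.
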